### Statistical Analysis

Statistical analyses will be conducted using Stata (version 19; StataCorp). Continuous variables will be described using means and SDs when normally distributed; for skewed distributions, medians and IQR will be reported. Normality will be assessed using visual inspection of histograms and quantile-quantile plots and confirmed with the Shapiro-Wilk test.

Comparisons of continuous variables between groups (eg, before vs after the intervention and intervention vs control regions) will be performed using the Student *t* test or the Mann-Whitney *U* test, as appropriate. The Student *t* test is a statistical method used to determine whether the means of 2 independent groups are significantly different from each other. It assumes that the data in each group are approximately normally distributed and that the variances are equal or similar.

Categorical variables will be summarized as absolute frequencies and percentages. Between-group comparisons will be conducted using chi-square tests or Fisher exact tests.

All statistical comparisons will be 2-sided, and results will be considered statistically significant if *P*<.05. Corresponding 95% CIs will be reported for all estimated parameters.

The primary outcome analysis will assess the difference in stroke incidence before and after the 2-year intervention period among residents of precarious neighborhoods within the CACL of French Guiana. Stroke incidence, derived from PMSI hospitalization data, will be compared across the 2 periods using the chi-square test. To evaluate temporal trends and detect structural breaks attributable to the intervention, segmented regression of interrupted time series (ITS) [33] data will be applied. The ITS model will estimate the immediate change in level and the change in slope after the intervention, while adjusting for autocorrelation and seasonality as necessary based on model diagnostics (Figure 3).

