The primary approach uses the chi-square test; approximately 350 patients with stroke are admitted annually to the Centre Hospitalier de Cayenne, with 68% (n≈238) occurring among socioeconomically precarious patients. Assuming the intervention leads to a 30% reduction in stroke incidence within this population—consistent with previous international interventions—a postintervention count of approximately 167 strokes per year (a reduction from 238) is anticipated. To detect this effect with 90% power at a 5% significance level (α=.05) using a 2-sided chi-square test comparing proportions before and after the intervention, a minimum of 367 cumulative postintervention stroke cases over a 2-year period is required.

Second, a segmented regression (ITS) analysis will be used to complement the chi-square test by examining both immediate level changes and slope changes after the intervention. On the basis of 60 monthly preintervention observations (5 years) and 24 monthly postintervention observations (2 years), and assuming autocorrelation (ρ=0.3-0.5) typical of health administrative data, this design provides adequate power (>80%) to detect a change in slope corresponding to a 20% to 30% reduction in incidence, assuming a baseline coefficient of variation of 15% to 20% in monthly stroke counts.

The chi-square test provides a straightforward test of the primary hypothesis, while ITS analysis accounts for underlying temporal trends and potential confounders, offering a more nuanced understanding of intervention effects. Both analyses will be reported, with ITS serving as the primary confirmatory analysis and the chi-square test as a sensitivity check.

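### The chi-square test has conflicting roles in the primary analysis, no single ITS effect is named as decisive, and the chi-square check assumes an independence that the plan itself denies

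*Protocol article*

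**What the plan says.** All of this stands in the Statistical Analysis section of the protocol article.

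- In the paragraph on the primary outcome: "Stroke incidence, derived from PMSI hospitalization data, will be compared across the 2 periods using the chi-square test". Segmented regression follows, to look at temporal trends and breaks: "The ITS model will estimate the immediate change in level and the change in slope after the intervention". Adjustment for autocorrelation is mentioned for this model only.
- In the sample-size text: "The primary approach uses the chi-square test", with 367 cumulative postintervention strokes required for 90% power at a two-sided 5% level.
- Next, "a segmented regression (ITS) analysis will be used to complement the chi-square test", with power above 80% stated for a slope change only, "assuming autocorrelation (ρ=0.3-0.5) typical of health administrative data" and a monthly coefficient of variation (CV) of 15% to 20%.
- In the closing paragraph: "The chi-square test provides a straightforward test of the primary hypothesis", and then the ranking: "Both analyses will be reported, with ITS serving as the primary confirmatory analysis and the chi-square test as a sensitivity check".

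The section sets a general two-sided threshold of P<.05. It does not say whether level, slope, a joint test or an average effect settles the primary objective.

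**The concern.** There are three linked problems.

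1. **Conflicting roles.** The chi-square test is given the work of a primary analysis in several places and is then ranked as a sensitivity check. The only explicit event target belongs to the analysis ranked second.
2. **No deciding effect.** Level and slope can disagree, for example a drop at launch followed by a rising slope. The text does not say how such a result would be read, or which coefficient must be significant.
3. **A weak check.** A before/after test that treats the strokes as independent counts conflicts with the autocorrelation assumed a few sentences away. It also takes no account of a trend already under way. Its agreement with the ITS could reflect either feature rather than the intervention.

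The design is nonrandomized and in one region, and the Discussion already anticipates a significant reduction. A criterion fixed in advance is therefore a main protection against selective reading.

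**Working it through.** **Inputs from the document.** 60 pre- and 24 postintervention months; 238 strokes a year, so m = 238/12 = 19.83 a month; 30% reduction; two-sided 5%, 90% power; ρ = 0.3 to 0.5; CV = 15% to 20%.

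**1. The plan's own figure.** With rate ratio r = 0.7, and k the ratio of pre- to postintervention time, the usual formula for two Poisson rates gives postintervention events = r(1.96 + 1.2816)²(r + 1/k)/(1 − r)², where (1.96 + 1.2816)² = 10.51.
- Equal periods (k = 1): 0.7 × 10.51 × 1.7/0.09 ≈ 139.
- Five years against two (k = 2.5): 0.7 × 10.51 × 1.1/0.09 ≈ 90.

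The figure of 367 is not reproduced. The plan's own effect gives 2 × 0.7 × 238 = 333 postintervention strokes, fewer than 367. This is a separate matter, and nothing below depends on it.

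**2. Level or slope.** The segmented model has intercept, trend, level change and slope change. It was fitted by generalised least squares with a known AR(1) covariance over 84 months.
- The correlation of the level and slope estimates is −0.59 (ρ = 0.3) and −0.54 (ρ = 0.5) if postintervention months are numbered from 1, and −0.55 and −0.49 if numbered from 0.
- The bivariate normal chance that at least one |z| exceeds 1.96 is 8.8% to 9.1%. The bound for independent estimates is 1 − 0.95² = 9.75%.
- The choice also changes power. For 20% to 30% reductions over the plan's CV and ρ range (months numbered from 0), power is 32% to 91% for a level change, 15% to 60% for a slope that reaches the reduction at month 24, and 46% to 99% for a slope that averages it over 24 months.

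**3. True size of the before/after test.** Let D be the difference in monthly means.
- Under independence, Var(D) is proportional to 1/60 + 1/24 = 0.0583. Under AR(1) it is 0.1050 (ρ = 0.3) or 0.1642 (ρ = 0.5), which is 1.80 or 2.81 times as large.
- The count test takes the monthly variance to be m. The plan's CV implies CV²m², a ratio of CV²m = 0.446 (CV 15%) or 0.793 (CV 20%).
- With f the product of the two ratios, size = 2[1 − Φ(1.96/√f)].

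| CV | ρ | f | True size at nominal 5% |
|---|---|---|---|
| 15% | 0.3 | 0.803 | 2.9% |
| 15% | 0.5 | 1.256 | 8.0% |
| 20% | 0.3 | 1.428 | 10.1% |
| 20% | 0.5 | 2.233 | 19.0% |

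**4. Prior trend.** The document gives no trend, so annual declines of 1%, 2% and 3% are assumptions. Other conditions are independent Poisson counts, 238 a year at the start and no intervention effect. The window midpoints lie at 2.5 and 6 years, 3.5 years apart, so the apparent rate ratio is about (1 − g)^3.5. Rejection rates are from simulation of the conditional 24/84 test.

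| Annual decline g | Expected strokes, pre / post | Apparent rate ratio | Rejection |
|---|---|---|---|
| 1% | 1161 / 448 | 0.97 | 9.46% |
| 2% | 1132 / 422 | 0.93 | 23.6% |
| 3% | 1104 / 397 | 0.90 | 45.2% |

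A hand check for 3%: z = 0.1074/√(1/1104 + 1/397) = 0.1074/0.0585 = 1.84, and Φ(1.84 − 1.96) ≈ 45%.

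**The case against.** The best defence is that a ranking exists. The closing sentence makes the ITS confirmatory and the chi-square a sensitivity check, and the phrase about a primary approach belongs to the sample-size text. This stands. A reader might infer that success could be claimed on the chi-square result alone, but the closing ranking does not allow that. What remains is text that disagrees with the ranking.

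Second, a statistical analysis plan that is not shown may name the tested contrast, and the power sentence points towards slope. That is fair as far as it goes. A reader might take 9% as the trial's actual error rate, but the document never says that either coefficient suffices. A joint test or one pre-named coefficient would hold 5%. The gap is still visible in the text: two effects are to be estimated, one is powered, and neither is made decisive.

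Third, the chi-square test is not always too liberal. At CV 15% and ρ = 0.3 it is conservative. That happens because 15% lies below the Poisson CV of 1/√19.83 = 22.5%. At the Poisson CV the size would be 14% to 24%, but that CV lies outside the plan's stated range, so those figures are not used here.

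Fourth, the trend figures rest on assumed declines. The ITS is meant to handle trend, and Strengths and Limitations already names secular trends and proposes comparison regions. The figures therefore bear only on what the simple check can corroborate.

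Finally, a reader might count the admission about imprecise denominators, under Intervention or Treatment, against the chi-square test. That passage concerns screening coverage, not the denominator for hospital stroke incidence.

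**Conclusion.** The concern holds in this limited form. The text conflicts on the role of the chi-square test, although its last sentence does rank the two analyses. The confirmatory ITS has two effect parameters and no deciding one, and type I error would be about 9% if either could count. The chi-square check contradicts the plan's own autocorrelation. Its true size is about 3% to 19% over the plan's CV and ρ range, above 5% in three of four corners, and it cannot separate an effect from a prior trend.

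The size figures assume AR(1) errors, a normal approximation and no trend or seasonality. The 9% also assumes a known covariance. The trend figures assume independent Poisson counts and declines that the document does not give. The chi-square faults weigh less than the missing deciding contrast, because that test is finally ranked as a sensitivity check.

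**What to change.** 1. Make the primary-outcome paragraph and the sample-size text agree with the closing ranking: ITS confirmatory, before/after comparison as sensitivity check. State which analysis each power figure belongs to.
2. Name one confirmatory ITS contrast, tested once at two-sided 5%. One reasonable choice is the modelled average rate ratio over the 24 postintervention months against the projected preintervention trend. Report level and slope descriptively, and give power for the named contrast.
3. Replace the chi-square sensitivity check with a before/after quasi-Poisson or negative binomial rate ratio with autocorrelation-robust standard errors. Describe it as not adjusted for trend.

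The cost is wording plus one power calculation; the data and software stay the same. The simple before/after comparison will generally have a wider interval. The Results section expected the primary analysis in April to May 2026, and the article is dated August 2026. It does not say whether the analysis has been run. If outcome data have already been analysed, the choice of contrast should be dated and disclosed.

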### Ethical Considerations

The study protocol has been reviewed and approved by the Comité de Protection des Personnes (CPP) South Mediterranean I, on January 11, 2023 (reference number SI 22.01568.000191 and national number ID-RCB 2022-A026000-43; category 3 minimal risk research). The study was registered on ClinicalTrials.gov on April 24, 2023 (NCT05814068).

All participants receive oral information about the study’s objectives, procedures, the voluntary nature of participation, and their rights. Written informed consent will not be sought because of high illiteracy rates in the target population. Rather, trained mediators document participants’ nonopposition to participation after ensuring comprehension through an oral explanation in the participant’s preferred language. Multilingual mediators and translation services ensure accessibility. The study adheres to the ethical principles outlined in the Declaration of Helsinki and complies with French data protection legislation (Loi Informatique et Libertés, modified on August 6, 2004) and the European General Data Protection Regulation (GDPR, 2016/679). A Data Protection Impact Assessment was completed prior to study initiation. Data are deidentified before analysis using a unique study identifier, with the correspondence table stored securely and separately from the research data. Access is restricted to authorized personnel only. Participants may withdraw at any time without justification and without affecting access to usual medical care. The promoter (Centre Hospitalier de Cayenne) has declared this research to the Commission Nationale de l’Informatique et des Libertés (CNIL) under simplified declaration procedures for health research (*méthodologie de référence* MR-003), with the engagement dated December 21, 2021.

## Results

This study was funded in 2022 and registered on ClinicalTrials.gov in April 2023 (NCT05814068). Recruitment for this study began in September 2023 and concluded on September 4, 2025, marking the end of the 24-month intervention period. During this period, 23,289 participants benefited from the intervention (ie, received at least 1 BP measurement and health education session), including 10,901 (46.8%) who completed the full enrollment questionnaire. Three-month telephone follow-up for participants with elevated BP was conducted as scheduled and completed by December 2025. Case report form (CRF) data entry and quality monitoring procedures were in progress as of February 2026, with database lock planned for March 2026 and primary outcome analysis expected between April 2026 and May 2026.

## Discussion

### Principal Anticipated Findings

This community-based hypertension screening intervention in French Guiana’s precarious neighborhoods is anticipated to demonstrate a significant reduction in stroke incidence among socioeconomically vulnerable populations. On the basis of the comprehensive deployment of trained health mediators who screened >23,000 participants across 32 neighborhoods, we expect to observe a 20% to 30% reduction in stroke incidence in the 2-year postintervention period compared to the 5-year baseline period. If confirmed, this would represent one of the largest quasi-experimental demonstrations of stroke prevention through community-based hypertension screening in a low- to middle-income setting in Amazonia. It is anticipated that the intervention will also result in a significant decline in other cardiovascular and renal events compared to the preintervention period.

### Comparison to Prior Work

By targeting underserved neighborhoods and using trained health mediators, the project introduces an innovative strategy that complements current health service models.

The anticipated outcomes of this community-based hypertension screening intervention are expected to align with previous studies indicating that population-level hypertension control can reduce stroke incidence significantly [37]. It is anticipated that the proposed intervention’s impact will meet or exceed this reduction given its specific focus on vulnerable populations with a high baseline prevalence of uncontrolled hypertension and limited access to care [38-40].

Unlike prior interventions that often lacked integration into existing community health infrastructure, this project’s use of local health mediators may enhance referral adherence and treatment initiation, addressing a common limitation cited in prior studies, in which more than 40% of referred patients failed to access follow-up care [24,27]. Furthermore, although previous programs reported limited sustainability because of their reliance on nonintegrated, short-term staff, this study’s design aims to improve scalability through embedded community-based actors [24]. Thus, the expected findings will provide valuable comparative data for existing models and address gaps in stroke prevention strategies, particularly in socially underserved urban settings in low- and middle-income regions [37].

Beyond disease incidence, the study will assess adherence to medical referrals, satisfaction with the program, and changes in antihypertensive treatment patterns, with the objective of generating scalable insights for health policy and population-level prevention strategies.

### Strengths and Limitations

This study has several important strengths. First, the use of comprehensive administrative hospitalization data (PMSI) for the primary outcome eliminates selection bias in outcome ascertainment, as all stroke hospitalizations in the region are systematically captured regardless of participants’ awareness of the intervention. Second, the large-scale, community-based approach targets an entire socioeconomically vulnerable population across neighborhoods over 24 months, providing real-world evidence of intervention feasibility and reach. Third, the use of trained community health mediators from the same cultural backgrounds as the target populations enhances intervention acceptability and reduces barriers related to language and trust. Fourth, the 5-year preintervention baseline period and ITS analysis allow a robust assessment of temporal trends and intervention effects while controlling for underlying changes in stroke incidence.

However, several limitations must be acknowledged. The quasi-experimental design without randomization means that temporal confounders (such as concurrent public health campaigns, changes in health care access, or secular trends in treatment patterns) may influence outcomes independently of the intervention. Although we will attempt to control for these through comparison with nonintervention regions in French Guiana, unmeasured confounding remains possible. Reliance on administrative datasets, while ensuring comprehensive capture, may be subject to coding inaccuracies or changes in diagnostic practices over time. However, the use of validated *International Statistical Classification of Diseases and Related Health Problems, 10th revision* (ICD-10) codes for stroke diagnosis and the consistency of PMSI reporting requirements over the study period minimize this concern. Implementation heterogeneity across neighborhoods (varying in size, accessibility, and population composition) may introduce variability in intervention dose and reach. We will document coverage rates by neighborhood and explore heterogeneity in subgroup analyses, but differences in how intensively the intervention was implemented across neighborhoods may influence the results. For secondary outcomes assessed through participant questionnaires and telephone follow-up (eg, referral adherence, treatment initiation, and satisfaction), self-reported data may be subject to social desirability and recall biases. Additionally, loss to follow-up during the 3-month telephone interviews may affect internal validity for these secondary end points, although we plan to use multiple imputation techniques and will report sensitivity analyses restricted to complete cases. These limitations, however, do not affect the primary outcome analysis, which relies exclusively on objective administrative data. Finally, the exclusion of individuals under legal protection (eg, guardianship) is required by French research regulations but may reduce generalizability to populations with severe cognitive impairment or psychiatric conditions, groups that may also experience an elevated risk of cardiovascular disease. Despite these limitations, this study addresses a critical gap in stroke prevention research in underserved populations and will provide valuable evidence on the effectiveness and scalability of community-based hypertension screening in resource-limited settings.

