Despite promising results, several limitations persist in the evaluation of the impact of community-based hypertension screening on stroke incidence [16,17]. Many studies lack robust control groups or use cross-sectional designs, limiting causal inference [18-20]. Self-reported data and office-based BP measurements introduce recall and diagnostic bias, respectively [17,21,22]. Additionally, in socially vulnerable populations, low follow-up rates and limited integration with existing health infrastructure restrict program sustainability [23,24]. Few large-scale studies in low-resource settings, particularly in South America, have analyzed long-term cardiovascular outcomes such as stroke or end-stage renal disease (ESRD), using validated hospitalization data [25,26]. Moreover, evidence is sparse on adherence to referrals and longitudinal prescription patterns following screening, indicating an underexplored area for assessing the intervention’s impact [27].

To address the critical gap in longitudinal data on stroke prevention in low-resource settings, this prospective, community-based, quasi-experimental study was designed to evaluate the impact of decentralized hypertension screening on stroke incidence among adults aged ≥18 years residing in socioeconomically precarious neighborhoods within the Communauté d’Agglomération du Centre Littoral (CACL) region of French Guiana. Using mobile health stations and home visits, trained health mediators will conduct standardized BP assessments and educational interventions, linking individuals with elevated readings to appropriate health care services. The main outcome—hospital-based stroke incidence—will be measured using national administrative datasets, offering novel insights into population-level vascular risk mitigation in underserved communities.

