**Figure 1 figure1:**
[figure not shown]
Participant workflow during the study.

All interested participants receive a brief health education session covering hypertension awareness, associated dietary and lifestyle recommendations, and guidance on accessing health care entitlements. Participants may also be referred to other health care facilities or professionals in the event of health concerns other than hypertension. Subsequently, each participant undergoes standardized BP measurement using 3 readings spaced 1 to 2 minutes apart, including at least 1 reading from each arm, in accordance with European guidelines. If BP values suggest possible hypertension, participants are referred for medical evaluation either to a local physician or to the Permanence d’Accès aux Soins de Santé (PASS) based on their insurance status.

Suspected cases are provided with a formal referral document detailing the observed metrics to facilitate continuity of care within the health care system.

Participants identified with elevated BP are contacted by telephone at 3 months after inclusion (with an allowable variation of ±1 week) to assess diagnostic follow-through, treatment initiation, and compliance with medical recommendations. During this follow-up, mediators reinforce the importance of ongoing care if lapses are identified.

In parallel, after the mediators have provided oral information about the study, they verify the inclusion (age ≥18 years, residence in the CACL, and absence of legal protection) and exclusion criteria and obtain the participant’s nonopposition to participation. For these participants, an additional structured questionnaire is administered to collect sociodemographic and anthropometric data, cardiovascular history, prior diagnoses, medication adherence, barriers to health care access, and a satisfaction survey.

Withdrawal from the study is permitted at any time without justification and does not affect access to usual medical care. Investigators may also discontinue participation if continued participation is deemed not to be in the participant’s best interest. Reasons for withdrawal or loss to follow-up will be recorded when available.

Figure 2 outlines the stepwise procedure for participant inclusion, assessment, and subsequent actions based on BP results and health insurance status, including interventions, referrals, and follow-up steps.

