### Randomization and Blinding

Because this study is nonrandomized and uses a quasi-experimental design, no randomization procedures will be used. Participants will be naturally exposed to the intervention as a function of their geographic residence. To limit assessment bias, the primary outcomes will be based on objective administrative data from hospital discharge records and national health insurance datasets. These datasets are not influenced by participants’ awareness of their inclusion in the study.

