### Intervention or Treatment

The intervention will consist of a comprehensive, community-delivered hypertension screening and education program. It will be implemented by 12 trained health mediators organized into 3 teams of 3 to 4 mediators each. The protocol stipulates that each mediator can screen approximately 10 people per day, representing a target of 2000 adults per month. These mediators, certified through a university-level diploma in health mediation or with equivalent field experience, will engage directly with residents in all precarious neighborhoods within the CACL. Each neighborhood will receive at least 1 intervention visit during the 24-month intervention period. The number of visits per neighborhood will be determined based on population size and accessibility. The goal is comprehensive coverage of an estimated population of 50,000 adults in the target neighborhoods.

To maximize reach, each visit will last 1 to 2 days, with mediators establishing fixed screening posts and conducting door-to-door outreach. The quantification of coverage will not be based solely on the number of individuals screened but on the number of neighborhoods fully investigated by the mediators. The intervention will be considered complete for a neighborhood when the minimum number of planned visits has been conducted, when mediators have systematically covered all streets or sectors through door-to-door approaches, or when repeated visits yield diminishing returns.

Given population mobility and the informal nature of precarious settlements, we acknowledge that precise denominator estimation is challenging. Mediators will set up mobile stations or conduct home visits to measure BP triadically according to European guidelines, provide personalized health education focused on hypertension and lifestyle modification, assess health insurance coverage, and guide participants with elevated BP to appropriate health care professionals or social services (eg, general practitioners or the PASS unit). Follow-up will include a structured telephone call 3 months later to assess completion of the medical referral process.

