### Data Collection Tools

BP will be measured using validated electronic arm-cuff devices following standardized procedures: 3 measurements at 1- to 2-minute intervals after 5 minutes of rest, recording systolic and diastolic pressure in both arms following the European Society of Hypertension guidelines. Mediators document results immediately on structured forms and provide participants with referral slips if indicated. Sociodemographic, anthropometric, and medical history data will be collected using a paper-based questionnaire estimated to require 30 minutes per participant. The questionnaire included demographic data (age, sex, country of birth, languages spoken, and duration of residence), medical history (previous hypertension diagnosis, current medications, and cardiovascular events), health care access (insurance status, usual source of care, and barriers to access), and lifestyle factors (smoking, alcohol consumption, physical activity, and dietary habits). For participants with suspected hypertension, a standardized 3-month phone follow-up will be performed using a semistructured script to capture referral completion and treatment adherence. Administrative data on hospitalizations, diagnoses, and prescriptions will be accessed from the regional PMSI [32] and national health insurance databases. PMSI is a French hospital discharge database that compiles standardized clinical and administrative information on all inpatient stays in both public and private hospitals. It includes data such as patient demographics, diagnoses, medical procedures, and length of hospital stay. This system enables the construction of patient cohorts based on variables such as age, sex, comorbidities, and disease severity. Data are routinely collected from health care facilities, ensuring comprehensive population coverage and minimizing selection bias. Its use is governed by strict ethical and data protection regulations. No biological samples will be collected.

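### Complete hospital discharge data do not eliminate ascertainment bias when the program itself can change which strokes reach hospital

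*Protocol article*

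**What the plan says.** The Background section names the main outcome as "hospital-based stroke incidence". According to Data Collection Tools, the source is PMSI, which "compiles standardized clinical and administrative information on all inpatient stays in both public and private hospitals".

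The intervention does more than measure blood pressure. The workflow text under Study Design and Setting says that all interested participants receive "guidance on accessing health care entitlements", and that they may be referred elsewhere for other health concerns. Under Intervention or Treatment, mediators also "assess health insurance coverage, and guide participants with elevated BP to appropriate health care professionals or social services". Comparison to Prior Work describes the target population as having "limited access to care".

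Strengths and Limitations then claims that "the use of comprehensive administrative hospitalization data (PMSI) for the primary outcome eliminates selection bias in outcome ascertainment", giving as the reason "as all stroke hospitalizations in the region are systematically captured" whether or not participants are aware of the intervention. Randomization and Blinding is more careful: "To limit assessment bias, the primary outcomes will be based on objective administrative data from hospital discharge records". The limitations paragraph does list changes in access to care, but as a temporal confounder acting independently of the intervention, to be handled by comparison with nonintervention regions of French Guiana.

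**The concern.** The reason given supports complete capture of stroke admissions. The claim is about ascertainment of the outcome, and the outcome is interpreted as stroke incidence. The two agree only if the share of strokes that are admitted is the same before and after the program starts. A program that helps people obtain coverage and reach care can raise that share, particularly for mild strokes. TIA, PAD and aneurysm are open to the same effect, since more medical evaluation can produce more diagnoses.

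A rise in capture would hide part of a true fall in strokes. A flat or weak result could then mean no prevention, or prevention partly offset by better capture, and the total count alone could not separate the two. For the secondary outcomes, a rise in admissions could be misread as failure, although the Discussion anticipates a decline in other cardiovascular and renal events.

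**Working it through.** **1. Can the planned analyses remove the shift?**
- ITS adjusts for the preintervention trend. A capture shift caused by the program begins with the program, so it falls into the same level and slope terms that estimate the effect. If capture grows as contacts accumulate, it acts mainly on the slope.
- A nonintervention comparator removes changes common to both areas. A shift that the program produces where it runs is not common to both.
- The coding caveat in the limitations concerns how admitted strokes are coded, not whether a stroke is admitted.

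**2. How large could it be through contacted people?**

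Inputs from the article:
- 23,289 people reached by the end of the 24 months (Results).
- About 50,000 adults in the target neighborhoods (Intervention or Treatment).
- Expected reduction of 20% to 30% (Principal Anticipated Findings).
- 350 × 0.68 = 238 hospitalized strokes a year in precarious patients (Statistical Analysis), which reproduces the article's figure.

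Assumptions, because the article gives no capture shares: baseline capture *a*; contacts accrue linearly; contacted people have average stroke risk; nobody else changes behavior; and, as the extreme case, every contacted person's capture rises to 100%.

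Final reach = 23,289 / 50,000 = 0.466. Average reach over the 24 months = 0.466 / 2 = 0.233.

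Average capture after the start: *b* = *a* + 0.233 × (1 − *a*). Observed rate ratio = true rate ratio × *b*/*a*.

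| Baseline capture *a* | *b* | *b*/*a* | True 20% shows as | True 30% shows as |
|---|---|---|---|---|
| 0.90 | 0.923 | 1.026 | 17.9% | 28.2% |
| 0.85 | 0.885 | 1.041 | 16.7% | 27.1% |
| 0.80 | 0.847 | 1.058 | 15.3% | 25.9% |
| 0.70 | 0.770 | 1.100 | 12.0% | 23.0% |

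For example, with *a* = 0.85: 0.85 + 0.233 × 0.15 = 0.885; 0.885 / 0.85 = 1.041; 0.80 × 1.041 = 0.833, a 16.7% reduction. Each row is the largest attenuation possible under these assumptions at that baseline.

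**3. What does that do to power?**

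This is a two-sided Wald test on the log rate ratio with 5 × 238 = 1,190 strokes before and 476 × RR after (2 × 238 = 476), ignoring trend and autocorrelation. It only shows how sensitive a simple two-period comparison is; it is not the power of the ITS.
- No shift: RR 0.80, power about 97%.
- *a* = 0.90: RR 0.821, 391 strokes after, standard error √(1/1190 + 1/391) = 0.0583, z = 0.198 / 0.0583 = 3.39, power about 92%.
- *a* = 0.85: RR 0.833, 396 strokes after, standard error 0.0580, z = 0.183 / 0.0580 = 3.15, power about 88%.

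**4. What would hide the effect completely?**

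A relative rise in capture of 1/0.80 − 1 = 25% for a true 20% reduction, or 1/0.70 − 1 = 43% for a true 30% reduction. None of the rows above reaches this.

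**The case against.** The strongest reply is that this is a possibility and not an observed fact. That stands. A reader might infer that the intervention does change how strokes are ascertained, but the article gives neither the share of strokes managed outside hospital nor any change in it. Only the weaker statement, that the program can change ascertainment, is supported. The remark on limited access also sits beside uncontrolled hypertension, not acute stroke admission, and the linkage step applies to people with elevated readings.

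A reader might also assume a population-wide rise in capture from 85% to 95%, which would shrink a true 20% reduction to 10.6% (0.80 × 0.95/0.85 = 0.894). The article's own reach does not support that through contacts alone. Even at final reach, a 10-point rise overall needs 0.10 / 0.466 = 21.5 points among contacted people, taking 85% to 106.5%. Only spillover, such as from the radio and flyer campaigns, or higher stroke risk among contacts could bring it closer, and the article quantifies neither.

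It is fair to add that Randomization and Blinding claims only to limit bias, that the hospital-based definition is open, and that the limitations mention changes in access, coding and diagnostic practice. The later sentence saying that limitations leave the primary outcome unaffected most naturally refers to self-report and telephone follow-up, so it should not be read as denying this problem. A rise in capture also works against the hypothesis and would not create a false benefit.

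What remains is narrow: an absolute claim that does not follow from its reason, and a program-induced pathway that the limitations omit.

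**Conclusion.** The claim that bias in outcome ascertainment is eliminated is not a property of this design. The article supports complete capture of hospitalized strokes. The program can change how many strokes become hospitalized, and the planned comparisons cannot remove such a shift.

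The likely direction is toward the null. The size is unknown. Through contacted people alone, and under the assumptions stated, a true 20% reduction would show as no less than about 16.7% if baseline capture is 85%, or 17.9% if it is 90%. Lower baseline capture, spillover or higher stroke risk among contacts would make the loss larger; incomplete response among contacts would make it smaller. This matters for interpreting an attenuated or null result and does not undermine a clearly positive one.

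A reader might go further and treat a flat total with falling severe strokes as proof of changed capture. That does not follow: reduced severity, a subtype-specific effect or changing length of stay could give the same pattern.

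**What to change.** - **Strengths and Limitations, strengths paragraph:** limit the claim to complete capture of hospitalized strokes and drop the statement that bias is eliminated.
- **Limitations paragraph:** add intervention-induced change in hospital capture as a limitation of the primary outcome and of the hospital-based secondary outcomes, and say that nonintervention comparators and ITS do not remove it.
- **Supportive analysis from the same PMSI extract:** add an ITS on strokes less dependent on care seeking, for example intracerebral haemorrhage, stroke with in-hospital death, or stroke with a long stay. Report the short-stay share and the TIA-to-stroke ratio before and after. Data Collection Tools says PMSI holds diagnoses and length of stay.
- **Interpretation:** present these as sensitivity evidence on ascertainment, with no fixed rule that reinterprets a null primary result. The Results section expected the primary analysis in April to May 2026; if it has been run, label the additions post hoc.

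The cost is wording plus a few runs on data already in hand. The severe-stroke series will have fewer events and wider intervals, and in-hospital death and length of stay can themselves change with earlier presentation or changing practice.
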